### Study Drug

Cymbalta® (Duloxetine Delayed-Release Capsules) is a selective serotonin and norepinephrine reuptake inhibitor (SSNRI) for oral administration. Its chemical designation is (+)-(S)-N-methyl-γ-(1-naphthoxy)-2-thiophenepropylamine hydrochloride. The empirical formula is C18H19NOS·HCl, which corresponds to a molecular weight of 333.88. The structural formula is:

[figure not shown]

Duloxetine hydrochloride is a white to slightly brownish white solid, which is slightly soluble in water. Each capsule contains enteric-coated pellets of 22.4, 33.7, or 67.3 mg of duloxetine hydrochloride equivalent to 20, 30, or 60 mg of duloxetine, respectively. These enteric-coated pellets are designed to prevent degradation of the drug in the acidic environment of the stomach. Inactive ingredients include FD&C Blue No. 2, gelatin, hypromellose, hydroxypropyl

methylcellulose acetate succinate, sodium lauryl sulfate, sucrose, sugar spheres, talc, titanium dioxide, and triethyl citrate. The 20 and 60 mg capsules also contain iron oxide yellow.

Although the exact mechanisms of the antidepressant, central pain inhibitory and anxiolytic actions of duloxetine in humans are unknown, these actions are believed to be related to its potentiation of serotonergic and noradrenergic activity in the CNS.

Duloxetine is stored at 25°C (77°F); excursions permitted to 15-30°C (59-86°F). For Chicago Site: Study drug will be maintained in a locked cabinet in a locked room in Abbott Hall. A drug accountability log will be completed each time drug is dispensed or returned and will be maintained by the study coordinator. For Ohio Site: Study drug will be maintained in a locked cabinet in a locked room in NON's office complex. A drug accountability log will be completed each time drug is dispensed or returned and will be maintained by the [name], the site's study coordinator and [name], the site's study physician.

Treatment begins at 30 mg once daily for 1 week, to allow patients to adjust to the medication before increasing to 60 mg once daily. Some patients may respond to the starting dose. There is no evidence that doses greater than 60 mg/day confer additional benefit, even in patients who do not respond to a 60 mg dose, and higher doses are associated with a higher rate of adverse reactions. Before discontinuing patients, a gradual reduction in the dose rather than abrupt cessation is recommended. Patients will take 30 mg once daily for 1 week before cessation.

Duloxetine should be swallowed whole and should not be chewed or crushed, nor should the capsule be opened and its contents sprinkled on food or mixed with liquids. All of these might affect the enteric coating. Duloxetine can be given without regard to meals.

Duloxetine's matching placebo pellets are filled into size 1 blue/blue capsugel shells. Overall ingredients: empty gelatin capsules and Nu-Pareil sugar spheres. The matching placebo has a stability of 60 months with minimum allowable storage temperature limits: 15 degrees C/max allowed 25 degrees C. Do not refrigerate or freeze. Route of administration is oral.

Duloxetine is commercially available. Duloxetine and its matching placebo is provided free of charge by the Neuroscience Division of Lilly USA, LLC.

Duloxetine contains a black box warning for Suicidality (suicidal thoughts and/or self-harmful behavior). There is an increased risk of suicidality in children, adolescents, and young adults with major depressive or other psychiatric disorders.

The most common adverse events (happening in more than 5 of 100 people) are:

- Nausea
- Constipation
- Diarrhea
- Decreased appetite
- Dry mouth
- Sweating or night sweats
- Dizziness
- Headache
- Tiredness

- Weakness
- Drowsiness

Less common adverse events (happening in at least 2 of 100 people) include the following:

- Vomiting
- Stomach and/or abdominal pain
- Increased urination
- Difficulty urinating
- Blurred vision
- Fast or irregular heartbeat
- Weight changes
- Tremors (uncontrollable shaking of a part of the body)
- Changes in sexual desire or ability (see section below)
- Yawning
- Hot flashes
- Acid reflux
- Fever
- Hoarseness or sore throat
- Muscle pain or cramps
- Flu-like symptoms
- Seasonal allergy-like symptoms
- Upper respiratory infection
- Change in taste
- Anxiety or agitation
- Tingling at the fingers or toes, or general differences in sensation
- Rash
- Hives
- Itching

Rare adverse events (happening in 1 of 100 to 1 of 1000 people) include the following:

- Change in blood pressure
- Elevated liver enzymes

Serious adverse events that require immediate medical attention include the following:

- Unusual bruising or bleeding
- Pain in the upper right part of the stomach
- Swelling of the abdomen
- Yellowing of the skin or eyes
- Dark colored urine
- Extreme tiredness or weakness
- Confusion
- A combination of fever, sweating, confusion, and severe muscle stiffness
- Blisters or peeling skin
- Difficulty breathing or swallowing
- Swelling of the face, throat, tongue, lips, eyes hands, feet, ankles, or lower legs

- Worsening of depression-like symptoms
- Mania or hypomania (abnormally elevated mood, arousal, and/or energy-level)
- Withdrawal-like symptoms
- Serotonin syndrome (an adverse event that happens from taking certain combinations of medications; symptoms may involve increased heart rate, shivering, sweating, dilated pupils, intermittent tremor or twitching, changes in your reflexes, stiffness, and/or changes in bowels, blood pressure and body temperature)
- Neuroleptic malignant syndrome (similar to serotonin syndrome mentioned above, with the exception that neuroleptic malignant syndrome often involves a decrease in muscle tone and increased tiredness or weakness)
- Seizures
- Extrapyramidal symptoms (adverse events including extreme restlessness, involuntary movements, and uncontrollable speech)
- Damage to the liver
- High blood pressure resulting in organ damage
- Decreased level of sodium in the blood (could result in a coma)
- SIADH (inappropriate secretion of a natural hormone in the body that results in decreased sodium in the blood)
- Glaucoma
- Anaphylaxis (life-threatening allergic reaction)
- Stevens-Johnson syndrome (an adverse event that can lead to blistering of the mouth, palms, and/or soles)
- Erythema multiforme (a skin disorder due to an allergic reaction; may result in multiple circular, raised pink or red lesions)
- Exfoliative dermatitis (loss of the outer layer of skin)

### ***Randomization and Blinding Design***

For the first part of the study (Phase I), all patients will receive placebo. The design is single blinded; the participants will not know whether they are receiving active drug or placebo. The researcher, however, will know that they are all receiving placebo.

A one-to-one randomization will be used for drug vs. placebo in the second part of the study (phase II). The healthy controls will be matched to the treatment group by age, gender, and education. In addition, the double blind will be maintained throughout all study procedures.

### ***Study Endpoints***

Primary: Overall neocortical gray matter volume and regional gray matter density in patients treated with Duloxetine and placebo

Secondary: Changes in gray matter volume and regional density measures will be correlated with changes in pain parameters

Exploratory (Optional Visit): Differences in past experience and current expectations, as measured with the open-ended interview, will be

correlated to treatment response and to differences and/or changes seen in brain parameters

**Study Procedures (more detailed):**

Study visit procedures (for OA participants):

**PART ONE:**

- Visit 1: **Screening/Baseline Scan** (week 0) Medical history, physical examination, patient-reported outcome (PRO) battery of instruments (includes: a general health questionnaire (PHH), the short form of McGill Pain Questionnaire (sf-MPQ), WOMAC, and the Beck Depression Index (BDI)), the Pain detect questionnaire, and the Pain catastrophizing scale (PCS), pregnancy test (if female of child-bearing potential), complete a 15 minute MRI scan, dispense study drug.
- Visit 2: **Final visit/Scan2** (week 2) PRO battery, one 10 minute MRI scan, collect information on concomitant medications, collect unused rescue medications and empty study drug bottles

**PART TWO:**

- Visit 1: **Pre-Screening**. Medical history, physical examination, patient-reported outcome (PRO) battery of instruments (includes: a general health questionnaire (PHH), the short form of McGill Pain Questionnaire (sf-MPQ), WOMAC, and the Beck Depression Index (BDI)), the Pain detect questionnaire, and the Pain catastrophizing scale (PCS)
- Visit 2: **Screening/Baseline Scan**. Basic chemistry panel and complete blood count (CBC), pregnancy test for females of child-bearing potential, MRI scans
- Visit 3: **Randomization**. (Week 0) WOMAC, dispense Duloxetine/placebo (at 30mg/day) and rescue medications, collect information on concomitant medications
- Visit 4: **Interim Visit**. (Week 1 ± 3 days) Dispense drug/placebo (increase dose of duloxetine/placebo to 60 mg/day), WOMAC, collect AEs and concomitant medication information
- Visit 5: **Interim Visit**. (Week 6 ± 7 days) Dispense drug/placebo (same dose as in Visit 3), WOMAC, BDI, collect AEs and concomitant medication information
- Visit 6: **Interim Visit**. (Week 16 ± 14 days) Dispense drug/placebo (begin to gradually reduce dose via a down-titration of 30mg for 1 week), MRI scans, PRO battery, collect AEs and concomitant medication information; collect unused rescue medications and empty duloxetine/placebo bottles
- Follow-up: **Phone call**. (Week 18 maximum) Collect AEs and concomitant medication information, verify that participant has successfully stopped the drug/placebo

Optional: **Interview** (Week 20 and beyond): Ask a series of open-ended questions about participants' experiences with pain, overall mood and personality, and medical history; give questionnaires about personality and pain/medical beliefs and expectations

Control participants will only complete visits 2 and 6. More specifically, they will only complete the PHH (once during screening) and the BDI (at all visits). Urine dipstick pregnancy tests will only be done in healthy controls if the participant is a woman of child-bearing potential. No blood will be drawn. Control participants also have the choice of completing an optional visit at the very end of the study that involves answering questions in an open-ended interview and completing a set of new questionnaires that supplement this interview.

For part two of the study, high-resolution anatomic brain images and functional brain scans are collected before and after four-months of treatment with duloxetine in 30 OA patients, in 30 OA patients who receive placebo, and in 25 healthy controls. Brain morphology is contrasted between these two time points, across the three groups, for overall neocortical gray matter volume and regional gray matter density changes. Pain relief, based on questionnaire outcomes and the MPQ's VAS, are then used as covariates in both patient groups to identify the effect size of magnitude of pain relief on restoration of brain grey matter. The procedures follow exactly our publications on the topic (Geha et al., *Neuron*. 2008; 60: 570. [name] et al., *J. Neuroscience* 24:10410, 2004).

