For all of these scans, the participant only has to lie quietly and remain still in the scanner. Each scanning session (consisting of a total of two 10 minute scans) takes a little under 25 minutes to complete and is considered completely non-invasive. The only discomfort is the requirement that subjects lay still in the scanner for the duration. All patient participants complete a general health questionnaire (PHH), the short form of McGill Pain Questionnaire (sf-MPQ), the Western Ontario and McMaster Osteoarthritis Index (WOMAC), and the Beck Depression Index (BDI) at screening, the time of entry (baseline visit), and at the final scanning visit (visit 5). Only the WOMAC will be completed on interim visits three and four.

Healthy control participants will participate in part two of the study only. They will be asked to complete the PHH only at the screening visit (to make sure that there are no potential physical or mental comorbidities or confounding medications). They will be asked to personally complete the BDI at all visits, and they will have the same number and types of scans as OA participants.

All participants will also have the choice of completing an optional visit at the very end of the study that involves answering questions in an open-ended interview and completing a set of new questionnaires that supplement this interview. OA participants will be asked a series of questions about their chronic pain, mood, medical history, and medical beliefs which, depending upon how detailed their responses are, will last 30 minutes to an hour. After the interview, OA participants will be asked to fill out the Chronic Pain Acceptance Questionnaire (CPAQ), the Pain Sensitivity Questionnaire (PSQ), the Perceived Sensitivity to Medicine Scale (PSM), the Five-Factor Personality Index (NEO-FFI), and the Life Orientation Test, Revised version (LOT-R). Healthy participants will be asked a series of questions, most of which are the same as those for the OA and some of which are different and ask about acute painful experiences instead of chronic pain. There are less questions for healthy participants than OA participants, so depending upon how detailed their responses are, healthy participant interviews will last 20-40 minutes. After the interview, healthy participants will be given the PSQ, PSM, NEO-FFI, and LOT-R.

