Brain image data collection and analysis is done under [name] supervision, which will be performed double blinded. Brain scan data will be transferred to [name]'s lab where the automated brain morphometric analyses are performed. We contrast brain morphology using a 2-way analysis of variance, factor one is group (patients treated with drug, with placebo, and healthy controls), and factor two is repeat measure time of scan. A secondary analysis will involve correlating brain regional changes to pain (VAS score from sf-MPQ) and the other questionnaire outcomes.

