***Major inclusion criteria include:***

- \* Age: 45-80 years
- \* ACR criteria for OA including Kellgren-Lawrence radiographic OA grades II-IV
- \* VAS pain score  $\geq 5/10$  within 48 hrs of the phone screen and visit 1 (Screening)
- \* Knee OA for a minimum of 12 months
- \* Need for daily pain medication to manage symptoms of OA

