### ***Efficacy Assessment***

Efficacy will be assessed primarily through the utilization of the WOMAC indices, specifically those regarding changes in pain, functionality, and stiffness in the knee. In addition, changes in VAS scores (from the sf-MPQ) could also be used to measure the drug's efficacy with regard to pain relief. The BDI scores could also be used to measure emotional or cognitive changes associated with the active drug, and thus act as an assessment tool in this regard.

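### Two sections of the protocol disagree on when the sf-MPQ (with VAS) and BDI are collected in Part Two; under the detailed schedule the VAS has no value at the baseline scan or at randomisation

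*Protocol*

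**What the plan says.** Study Design has patients complete the general health questionnaire, sf-MPQ, WOMAC and BDI "at screening, the time of entry (baseline visit), and at the final scanning visit (visit 5", with only the WOMAC at interim visits three and four.

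The Part Two list under Study Procedures (more detailed) has six visits and a different pattern:

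- The full battery, including "the short form of McGill Pain Questionnaire (sf-MPQ), WOMAC, and the Beck Depression Index (BDI)), the Pain detect questionnaire, and the Pain catastrophizing scale (PCS", is given at Visit 1 (pre-screening).
- Visit 2 (screening and baseline scan) lists "Basic chemistry panel and complete blood count (CBC), pregnancy test for females of child-bearing potential, MRI scans" and no questionnaire.
- Visit 3 (randomisation) lists "Week 0) WOMAC, dispense Duloxetine/placebo (at 30mg/day) and rescue medications".
- Visits 4 and 5 have the WOMAC, with the BDI added at Visit 5.
- Visit 6 (week 16) has "MRI scans, PRO battery, collect AEs and concomitant medication information".

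The inclusion criteria require a VAS of at least 5/10 "within 48 hrs of the phone screen and visit 1 (Screening".

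The pain variable is described in several places. The image-analysis paragraph after the Part Two visit list says "A secondary analysis will involve correlating brain regional changes to pain (VAS score from sf-MPQ", along with other questionnaire outcomes. The closing paragraph of the detailed procedures uses pain relief from questionnaires and the VAS as a covariate in both patient groups. Statistical Analysis takes pain intensity from the VAS within the sf-MPQ. Efficacy Assessment says "Efficacy will be assessed primarily through the utilization of the WOMAC indices", which cover pain, function and stiffness. Sample Size Considerations expects a VAS fall of 10 to 20 mm from baseline.

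**The concern.** The two descriptions cannot both be followed. Study Design gives two pre-treatment sf-MPQ and BDI assessments; the detailed schedule gives one, at a visit where a high VAS is a condition of entry.

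A site working from the detailed schedule would never collect the baseline VAS that Study Design calls for. A statistical analysis plan cannot recover a score that was not taken.

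Three things would follow:

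- The expected fall from baseline would have no VAS at the baseline scan or randomisation to be measured from.
- VAS change from Visit 1 would include the fall that follows selection on a high score. Statistical Analysis means to use the placebo patients' pain measures to tell biological from psychological effects. The trial has no untreated osteoarthritis group (Part One patients all receive placebo, and healthy controls complete no pain scale), so this fall could not be separated from placebo response.
- Pain change would run from Visit 1 and scan change from Visit 2. The first Part Two visit list limits screening to randomisation to two weeks but sets no limit between Visits 1 and 2.

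**Working it through.** **Schedule.** Pre-treatment collection in Part Two according to each section:

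| Instrument | Study Design | Detailed procedures |
|---|---|---|
| sf-MPQ with VAS | screening and baseline visit | Visit 1 only |
| BDI | screening and baseline visit | Visit 1 only |
| WOMAC | screening and baseline visit | Visits 1 and 3 |
| Final battery | visit 5 | Visit 6 |

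Study Design numbers its visits as if there were five; both Part Two visit lists have six. Its baseline visit could therefore mean Visit 2 or Visit 3. On either reading it promises a second pre-treatment VAS that the detailed schedule does not list. The inclusion criterion adds an ambiguity by calling visit 1 screening, whereas the visit lists call Visit 1 pre-screening and Visit 2 screening.

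**Size of the regression to the mean.** The protocol gives the threshold (5/10, taken as 50 mm) and the expected fall (10 to 20 mm). It gives no mean, SD or retest correlation, so these are assumptions: SD 20 mm, source mean 50 to 60 mm, retest correlation r 0.5 to 0.8, normal scores and independent errors between visits.

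With selection at Visit 1 alone, the expected fall without any treatment is (1 − r) × SD × φ(z)/(1 − Φ(z)), where z = (50 − mean)/SD. For mean 50 and r 0.7, z = 0 and φ/(1 − Φ) = 0.399/0.5 = 0.798, so the fall is 0.3 × 20 × 0.798 = 4.8 mm.

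The criterion names the phone screen as well as visit 1. Requiring both to pass was simulated with 2 million draws per setting.

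| Mean (mm) | r | Visit 1 only (mm) | Phone screen and Visit 1 (mm) |
|---|---|---|---|
| 50 | 0.5 | 8.0 | 6.0 |
| 50 | 0.7 | 4.8 | 3.2 |
| 50 | 0.8 | 3.2 | 2.0 |
| 60 | 0.5 | 5.1 | 4.0 |
| 60 | 0.7 | 3.1 | 2.1 |
| 60 | 0.8 | 2.0 | 1.3 |

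Under the two-occasion rule the range is 1.3 to 6.0 mm. Against the expected fall that is between 1.3/20 = 6.5% and 6.0/10 = 60%. With wider assumptions (mean 40 to 70 mm, r 0.5 to 0.9) the two-occasion range at SD 20 mm is 0.4 to 8.4 mm. The one-occasion range at SD 15 to 25 mm is 0.3 to 13.4 mm.

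**Effect on the correlation.** The same simulation gave patients a true change with an assumed SD of 15 mm and correlated observed with true change. At mean 50 mm and r 0.7, with both occasions required, the correlation was 0.72 from Visit 1 and 0.70 from Visit 3. At r 0.5 it was 0.63 and 0.60. In no setting was it lower from Visit 1. Selection slightly narrows the spread of the Visit 1 error, and a shift common to all patients does not alter a correlation.

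**The case against.** The strongest reply is that little rests on this. Regression to the mean after selection before randomisation is expected equally in both arms, the primary endpoint is gray matter, and the secondary hypothesis is a correlation, not a test of mean VAS relief. The study calls itself exploratory. WOMAC pain is collected at randomisation, and the analysis text allows other questionnaires besides the VAS. No section says that VAS change starts at Visit 1, and Study Design points to a baseline score. All of this stands, and it limits the point to within-arm VAS relief, its interpretation and its timing.

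It does not remove the contradiction. The VAS is the pain measure named for the secondary analysis, and a score not collected under the detailed schedule cannot be supplied by a later definition of baseline.

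A reader might infer three stronger things, which the documents do not support:

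- That a Visit 1 baseline weakens the pain-brain correlation, more so on placebo, and so manufactures the predicted absence of correlation there. The simulation shows no such loss. A smaller mean relief on placebo does not by itself lower a correlation; a smaller spread would, but with either baseline.
- That the comparison of duloxetine with placebo is biased. Randomisation after selection rules this out in expectation.
- That pain is not measured at randomisation at all. That is true of the VAS and sf-MPQ, not of the WOMAC.

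Real drift in pain between Visit 1 and treatment could weaken the correlation, but nothing in the protocol allows it to be sized.

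**Conclusion.** The point holds as a contradiction in data collection with a limited statistical consequence. Under the detailed schedule, the only pre-treatment VAS comes from an entry-threshold visit at an unstated interval before the baseline scan. Within-arm VAS relief would be overstated by about 1 to 6 mm if both the phone screen and Visit 1 must pass. That figure rests wholly on the assumed mean, SD, retest correlation and independent errors; the true amount could be trivial or a sizeable share of the expected 10 to 20 mm. It is worth correcting because the loss would be permanent and the remedy nearly free.

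**What to change.** Reconcile Study Design with the detailed Part Two schedule:

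- Add the sf-MPQ (with VAS) and BDI at Visit 3, before the first dose.
- Correct the visit numbers in Study Design to the six-visit schedule, so that the final battery is at Visit 6.
- Compute VAS change from Visit 3 to Visit 6 and keep the Visit 1 score for eligibility only. If errors are independent between visits, the regression caused by selection then drops out of the change score. The gap between the baseline scan and the pain baseline is held to the two weeks already allowed between screening and randomisation.
- For any patient already past Visit 3, use WOMAC pain from Visit 3 as the baseline pain measure.

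The cost is a few minutes of questionnaires at an existing visit and a wording amendment.

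### The Visit 5 dispensing line refers back to the 30 mg/day visit instead of the 60 mg/day visit, and the week 18 cap on the follow-up call can fall before the drug has been stopped

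*Protocol*

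**What the plan says.** The Part Two list under Study Procedures (more detailed) gives the dose visit by visit:

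- Visit 3, week 0: "dispense Duloxetine/placebo (at 30mg/day) and rescue medications".
- Visit 4, week 1 ± 3 days: "Dispense drug/placebo (increase dose of duloxetine/placebo to 60 mg/day".
- Visit 5, week 6 ± 7 days: "Dispense drug/placebo (same dose as in Visit 3), WOMAC, BDI".
- Visit 6, week 16 ± 14 days: "begin to gradually reduce dose via a down-titration of 30mg for 1 week".
- Follow-up call, week 18 at the latest: "Collect AEs and concomitant medication information, verify that participant has successfully stopped the drug/placebo".

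The Study Drug section describes the regimen in words: "Treatment begins at 30 mg once daily for 1 week, to allow patients to adjust to the medication before increasing to 60 mg once daily". For the end of treatment it says: "Patients will take 30 mg once daily for 1 week before cessation".

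The shorter Part Two visit list under Study Design also raises the dose to 60 mg/day at Visit 4 and orders no change at Visit 5. It lets the taper that begins at Visit 6 run for one to two weeks, and it also caps the call at week 18.

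**The concern.** There are two separate faults in the same schedule.

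The first is the dose. Visit 5 is meant to continue the current dose but names the visit at which 30 mg/day was dispensed. It is the only text that says what to hand out at week 6. Drug is held and logged separately at the Chicago and Ohio sites, so each would have to resolve the conflict for itself. If the line were followed, the active arm would spend most of the treatment period at half the intended dose. The randomised comparison would remain unbiased for what was given, but the contrast would be diluted. The Sample Size Considerations section already expects only 10-20 mm of VAS relief with 30 patients per arm, so there is little to spare.

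The second is the follow-up call. It exists to confirm that the drug has been stopped, and it is the last scheduled contact at which adverse events are collected; the later interview is optional and lists no such collection. If Visit 6 falls late in its window, the latest permitted call day comes while the patient is still tapering. The Study Drug section advises gradual reduction and lists withdrawal-like symptoms among the events needing immediate attention, so the period around stopping is one in which events should be collected.

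**Working it through.** **Part 1: dose.** Day 0 is Visit 3. Each dose change is assumed to take effect on the visit day, with full adherence.

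Inputs from the detailed Part Two schedule: Visit 4 nominally day 7 (window 4-10), Visit 5 day 42 (35-49), Visit 6 day 112 (98-126). Doses are 30 mg/day from Visit 3, 60 mg/day from Visit 4 and, read literally, 30 mg/day from Visit 5.

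At nominal timing:

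- Regimen in the Study Drug section: 7 × 30 + 105 × 60 = 210 + 6,300 = 6,510 mg; 6,510 / 112 = 58.1 mg/day.
- Visit 5 read literally: 7 × 30 + 35 × 60 + 70 × 30 = 210 + 2,100 + 2,100 = 4,410 mg; 4,410 / 112 = 39.4 mg/day.
- Shortfall: 6,510 − 4,410 = 2,100 mg; 2,100 / 6,510 = 32.3%.

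Over the permitted windows, with V4, V5 and V6 as the visit days:

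- Shortfall = 30 × (V6 − V5). Planned dose = 30 × V4 + 60 × (V6 − V4) = 60 × V6 − 30 × V4.
- Smallest (V4 = 4, V5 = 49, V6 = 98): 49 days at half dose; 1,470 / 5,760 = 25.5%.
- Largest (V4 = 10, V5 = 35, V6 = 126): 91 days at half dose; 2,730 / 7,260 = 37.6%.

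The likely origin can be traced. The Study Design section still says "Only the WOMAC will be completed on interim visits three and four" and calls the final scan visit 5. In that numbering the interim visits at weeks 1 and 6 would be visits 3 and 4, so Visit 3 would be the week 1 visit at which the dose becomes 60 mg/day. The cross-reference would have been correct there. This is an inference; the protocol does not state it.

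**Part 2: follow-up call.** Inputs: Visit 6 on days 98-126, which is 29 possible days; taper of 7 days (Study Drug and the detailed schedule) or up to 14 days (visit list under Study Design); latest call 18 × 7 = day 126. Stop day = Visit 6 day + taper length.

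| Taper | Possible stop days | Visit 6 days with stop after day 126 | Largest overrun |
|---|---|---|---|
| 7 days | 105-133 | 120-126 (7 of 29) | 133 − 126 = 7 days |
| 14 days | 112-140 | 113-126 (14 of 29) | 140 − 126 = 14 days |

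At the nominal Visit 6 (day 112) the stop falls on day 119 or day 126, and there is no conflict. If Visit 6 is on day 126, the call is due no later than the day the taper begins.

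If week 18 is instead read as the whole week, days 126-132, the affected Visit 6 days fall to day 126 alone for a 7-day taper (126 + 7 = 133 > 132; 1 of 29) and to days 119-126 for a 14-day taper (119 + 14 = 133 > 132; 8 of 29).

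**The case against.** On the dose, the protocol as a whole leaves little doubt about what is meant. The Study Drug section gives 60 mg after the first week, the visit list under Study Design orders no change at Visit 5, and a step-down to 30 mg at Visit 6 makes no sense from 30 mg. The wording of the Visit 5 line itself signals continuation. On this view it is a one-digit slip, and the shortfall figures describe a regimen nobody intended. That stands as far as intent goes, and the figures should be read only as what literal compliance would cost. It does not make the line harmless, because it is a dispensing instruction in the more detailed of the two schedules.

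On the call, the protocol does not give week 18 as a day number, and the looser reading shrinks the problem considerably. Two of the three places that state a taper length agree on one week, so the two-week case is the weaker one. The counts are permitted days, not probabilities; nothing says how often Visit 6 will be late. A call made during the taper has also not done its job, so a careful site would ring again. All of this limits the size. It does not remove the conflict: some overlap remains on either reading of week 18, without any protocol deviation, and a second call would fall after the stated maximum. Day 126 is also the natural reading, since a visit at week 16 ± 14 days treats a week number as a point in time.

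The call timing has no bearing on the primary endpoint, because the final scan is taken at Visit 6, where the taper only begins.

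**Conclusion.** Both points hold, and both should be fixed.

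The Visit 5 line misstates the dose. The intended dose, 60 mg/day, is clear from the rest of the protocol, so the 32% shortfall at nominal timing (26% to 38% across the visit windows) is a worst case under literal compliance and full adherence, not the expected exposure. Its effect would be dilution of the drug-placebo contrast.

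The call cap conflicts with the Visit 6 window and the taper. With week 18 as day 126, treatment can end up to 7 days after the latest call day under a one-week taper, or up to 14 days under a two-week taper. The conflict arises only when Visit 6 is late in its window, and fewer days are affected if week 18 means the whole week. The consequence is a gap in safety follow-up, not a threat to the analysis. Sample size and power calculations are not involved.

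**What to change.** 1. In the Visit 5 line of the detailed Part Two schedule, refer to Visit 4 instead of Visit 3 and state 60 mg/day explicitly.
2. Bring the visit numbers in the Study Design questionnaire paragraph into line with the two Part Two visit lists.
3. State one taper length in the Study Drug section and in both visit lists. One week is already given in two of the three places.
4. Time the follow-up call from the end of the taper and remove the week 18 cap. With the present Visit 6 window, the call must be allowed to at least day 133 (week 19) for a one-week taper, or day 140 (week 20) for a two-week taper.

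The cost is wording changes and a short dispensing note to both sites. No visit or procedure is added.
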